## Abstract

**Background:**

Mechanisms underlying the associations between changes in the urban environment and changes in health-related outcomes are complex and their study requires specific approaches. We describe the protocol of the interdisciplinary UrbASanté study, which aims to explore how urban interventions can modify environmental exposures (built, social, and food environments; air quality; noise), health-related behaviors, and self-reported health using a natural experiment approach.

**Methods:**

The study is based on a natural experiment design using a before/after protocol with a control group to assess changes in environmental exposures, health-risk behaviors, and self-reported health outcomes of a resident adult population before and after the implementation of a time series of urban interventions in four contiguous neighborhoods in Paris (France). The changes in environmental exposures, health-related behaviors, and self-reported health outcomes of a resident adult population will be concurrently monitored in both intervention and control areas. We will develop a mixed-method framework combining substantial fieldwork with quantitative and qualitative analytical approaches. This study will make use of (i) data relating to exposures and health-related outcomes among all participants and in subsamples and (ii) interviews with residents regarding their perceptions of their neighborhoods and with key stakeholders regarding the urban change processing, and (iii) existing geodatabases and field observations to characterize the built, social, and food environments. The data collected will be analyzed with a focus on interrelationships between environmental exposures and health-related outcomes using appropriate approaches (e.g., interrupted time series, difference–in-differences method).

**Discussion:**

Relying on a natural experiment approach, the research will provide new insights regarding issues such as close collaboration with urban/local stakeholders, recruitment and follow-up of participants, identification of control and intervention areas, timing of the planned urban interventions, and comparison of subjective and objective measurements. Through the collaborative work of a consortium ensuring complementarity between researchers from different disciplines and stakeholders, the UrbASanté study will provide evidence-based guidance for designing future urban planning and public health policies.

**Trial registration:**

This research was registered at the ClinicalTrial.gov (NCT05743257).

## Background

It has become widely accepted that overall health and quality of life result from a complex interplay between individual (e.g., age, gender, and socioeconomic position) and contextual built and social characteristics of the environment in which individuals live (e.g., transport infrastructures, land use, food environment, and area-level deprivation) [1, 2]. Thus, urban planning choices can affect the health and well-being of the population and contribute to reducing or, in contrast, enhancement of social health inequalities. The impact of urban redevelopment in a neighborhood can vary considerably depending on the socioeconomic characteristics of populations and environments: in some cases, it may increase social health-related inequalities [3].

Many urban planning and design decisions aimed at improving urban living conditions have been developed in recent years [4]. For example, in the field of air quality, since the year 2000, low-emission zones have been defined in a number of European cities in response to concerns about air pollution and public health. Although such transformations have high political and financial costs, there have been few real-life assessments to date of the well-being and health effects of such environmental policies as well as the role of social health inequalities [5]. Associations between urban changes, environmental exposures, and health-related behaviors generally form a highly complex network involving numerous interactions [6]. More specifically, the mechanisms underlying the associations between changes brought about by urban interventions and changes in environmental risks and health-related behaviors remain understudied. Increased understanding of such mechanisms is needed to clarify the significance and role of specific modifiable determinants.

The natural experiment approach is a way to assess the health impacts of urban interventions and represents an opportunity for innovative research. The Medical Research Council (MRC, United Kingdom) defines a natural experiment as an approach “*which exploit(s) natural or unplanned variation in exposure, i.e., variation that is not manipulated for the purposes of research*” [7, 8]. In a recent “call to action” for the transition to health and sustainable cities, the authors recommended conducting natural experiments to assess the impact of urban interventions on health, social, environmental, and equity outcomes [2]. The natural experiment approach has already been well developed in other research disciplines such as economics. Joshua Angrist, Guido Imbens, and David Card shared the 2021 Nobel prize in economic sciences for their research based on this approach. They showed how causality can be inferred from observational data in real-world natural experiments, specifically regarding labor market issues. In other words, the natural experiment approach takes advantage of the circumstances in which relevant changes occur in a given area and population, e.g., an urban intervention, and then tries to plausibly attribute changes in outcomes of interest to the intervention [9]. Natural experiments are increasingly considered as being able to provide important new input in research and can be very useful for informing policy decisions [10].

In a recent systematic review, 15 studies describing natural experiments using changes in the built environment and investigating health-related consequences were identified. Eight of these reported (favorable) changes in active mobility and dietary intakes when measured on residents after one year post-baseline [4]. However, the authors highlighted that it is difficult to draw overall conclusions, especially because of methodological limitations such as a lack of a comparison group or limited sample sizes.

The main objective of the UrbASanté study is to assess how urban interventions can modify environmental exposures (including air quality, noise, food environment, built, and social characteristics), health-related behaviors, and self-reported health using a natural experiment protocol in Paris (France).

The specific aims of the project are (i) to develop a combination of methods to assess and monitor environmental exposures, health-risk behaviors, and self-reported health; (ii) to collect relevant data during experimentation at a local level in a real-life setting; and (iii) to analyze the data generated to better understand the effects of urban transformations on environmental exposures, health-risk behaviors, and self-reported health in order to more accurately guide public health and urban planning policies.

## Methods

### Study design

The study is based on a natural experiment approach with a before/after protocol design to assess changes in environmental exposures, health-risk behaviors, and self-reported health outcomes of a resident adult population before (T0) and after (T1) the implementation of a time series of urban interventions.

The changes observed in adult residents located in the intervention areas (“exposed population”) will be compared to those in adults living in control areas (“unexposed population”). Control areas are located close to areas with urban intervention sites but are not themselves subject to urban intervention. As described in Fig. 1, the data collection will be implemented in two stages in both the intervention and the control areas: a first stage at baseline (T0, 2022), and a second stage (T1, 2025) after the urban interventions.

**Fig. 1 Fig1:**
[figure not shown]
Overall design of the UrbASanté study. (adapted from Leatherdale et al., 2019)

#### Intervention and control neighborhoods

The UrbASanté study will examine potential changes in environmental exposures, health-related behaviors, and self-reported health due to urban interventions in an urban area called Porte de la Chapelle in the northern part of the city of Paris (France). This area includes four contiguous neighborhoods located in the northern part of the 18th arrondissement of Paris (Fig. 2).

This area exhibits specific characteristics compared to the broader Parisian conurbation: a large part of its population is socioeconomically deprived and it is exposed to high levels of pollutants [11]. This area is also defined as a place of interest in the context of the Olympic and Paralympic games scheduled to take place in Paris in 2024. Urban interventions will occur with different stages of transformation from 2024 (the Paris Olympic and Paralympic games) to 2030 (legacy of the Paris Olympic and Paralympic games) depending on each neighborhood.

Two neighborhoods will be referred to as “intervention” neighborhoods, with measures taken before and after a series of urban changes that will start in 2023 (Fig. 2).

The main urban changes in the Gare des Mines-Fillettes neighborhood (which includes the two urban sections of Charles Hermite and Valentin Abeille) will comprise the creation or renewal of urban green areas, pedestrian/cycle pathways and urban corridors, housing, redesigning of public spaces, and more specifically the construction of an Olympic sports facility.The urban changes in Porte de la Chapelle Avenue will mainly comprise the development of a new public transport network (bus) as well as the inclusion of cycle and pedestrian pathways and the widening of sidewalks.

Two neighborhoods will be referred to as “control” neighborhoods, with measurements at the same time periods as for the “intervention” neighborhoods.

Chapelle-international is a new neighborhood built on the site of a former railway wasteland. At the end of 2019, more than 1,500 residents had already moved into this neighborhood.The Chapelle-Evangile neighborhood will not undergo specific urban interventions, except in the northern part, where the renovation and expansion of a green area are currently being finalized.

**Fig. 2 Fig2:**
[figure not shown]
Intervention and control neighborhoods of the study area of the UrbASanté study

#### Resident data collection

In all studied neighborhoods, the criteria for inclusion will comprise: being an adult (18 years of age or older); residing in the neighborhood; and being able to read, write, or understand French well enough to complete the UrbASanté questionnaire (online or on paper) independently or with assistance from a research assistant. The UrbASanté study is conducted in accordance with the guidelines laid down in the Declaration of Helsinki, and all procedures have been approved by the Institutional Review Board of the French Institute for Health and Medical Research (CEI/IRB INSERM no. IRB00003888, IORG0003254, FWA00005831) and registered with the Commission Nationale de l’Informatique et des Libertés (2220971v0). All participants will provide informed consent. Participants will receive a 15 € voucher for returning a fully completed questionnaire.

#### Recruitment plan

We will use posters, flyers, social media, and local newspaper advertisements to raise awareness of the survey and increase enrollment, and we will develop a door-to-door recruitment protocol [12]. In a first step, the research team will identify the social housing providers, building superintendents for social housing buildings, and housing organizations for private buildings to be contacted prior to the field data collection. In a second step, we will set up appointments with building superintendents or private housing organizations to place posters announcing the study inside the buildings, and then a few days later, we will conduct the door-to-door surveys. The door-to-door surveys will aim to explain the UrbASanté study, distribute flyers and questionnaires, and collect email addresses for follow-up with inhabitants expressing interest in the research. In addition, we will organize information and survey sessions in the main lobby of the main buildings.

We will participate in a variety of community events and use social facilities (e.g., the local library) to conduct drop-in sessions, distribute the study questionnaire, and collect email addresses.

#### Mixed-method framework

Our analyses will make use of (i) collection of data relating to exposures and health-related outcomes among all participants and in subsamples, (ii) interviews with residents about their perceptions of their neighborhood and interviews with key stakeholders about the urban change processing, and (iii) existing geodatabases and field observations to characterize the built, social, and food environments (Fig. 3).

## Data collection

### Sampling plan

According to the 2018 census data from the INSEE (the French National Institute for Statistics and Economic Studies), 13,025 adults (≥ 18 years of age) reside in the entire study area (including the control and intervention neighborhoods). We will aim to recruit 600 adult participants at baseline to form the core data survey groups (300 in the intervention area and 300 in the control area). Although there is little precedent for sample size calculations for natural experiment studies (Kestens et al., 2019), potentially due to the multidimensionality of urban interventions, this sample size would be sufficient to assess a change in health-risk behaviors in the context of urban redevelopment. Indeed, assuming a power of 90% and an alpha of 0.05, 380 participants will be required to detect the effect reported by Pazin et al. (2016) for instance, i.e. an increase of 32 (95% CI: 15–51) min/week of walking after development of a new walking and cycling route [13].

In addition, we will aim to define three subsamples of participants to assess:

the nutritional quality of the household food supply through a food supply diary for a subsample among 400 participants (200 in the intervention area and 200 in the control area);the food provisioning practices of individuals through a semi-structured interview for a subsample of 30 participants (15 in the intervention area and 15 in the control area);the mobility-based real-time air pollution and noise exposures through sensor measurements for a subsample of 30 participants (15 in the intervention area and 15 in the control area).

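### The case for 600 participants states no clustering allowance and does not say what 380 counts, so 90% power holds only on one reading with almost no neighborhood clustering

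*Protocol article*

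**What the plan says.** The Sampling plan sets the size: "We will aim to recruit 600 adult participants at baseline to form the core data survey groups", split as "300 in the intervention area and 300 in the control area". It then asserts that "this sample size would be sufficient to assess a change in health-risk behaviors in the context of urban redevelopment". One calculation supports this: "assuming a power of 90% and an alpha of 0.05, 380 participants will be required to detect the effect", the effect being "an increase of 32 (95% CI: 15–51) min/week of walking after development of a new walking and cycling route", taken from a cited study and offered as an example.

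Four features of the design bear on that calculation:

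- **Timing.** Study design sets "a first stage at baseline (T0, 2022), and a second stage (T1, 2025) after the urban interventions", so change is measured over about three years.
- **Assignment.** Intervention and control neighborhoods names four contiguous neighborhoods, two in each condition. A resident's exposure follows from address.
- **Contrast.** Planned statistical analyses compares change in exposed residents with change in unexposed residents by difference-in-difference.
- **Model.** The same section gives multilevel regression as an example for relating environmental change to behavioral change.

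The Sampling plan gives no SD, sidedness, retention rate, ICC or design effect. It does not say whether 380 is the sum of both areas, the number per area or a single group measured twice.

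**The concern.** The 380 is the only quantitative support for the sample size, and the conclusion drawn from it is unconditional. A calculation that treats residents as independent overstates the information available when exposure varies only between neighborhoods. Residents of one neighborhood share local events that can move their walking together, and two neighborhoods per condition leave little to separate such shifts from the intervention.

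The undefined 380 matters too, because its possible meanings imply very different power for the planned contrast. The claim also extends from one walking effect to health-risk behaviors generally, with no calculation for any other behavior.

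At stake is the reading of the results. The Background criticizes earlier natural experiments for limited sample sizes. If this paragraph stands, a null difference-in-difference could be taken as coming from a study with 90% power.

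**Working it through.** **Inputs from the document:** effect 32 min/week; power 90%; alpha 0.05; 380 required; 600 recruited, 300 per area; four neighborhoods, two per condition.

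**Assumptions:** two-sided test; equal neighborhood sizes; loss of 0 to 30%; ICC of 0 to 0.02. The ICC is that of individual *change* in walking. The document gives no value for loss or ICC.

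**1. Reproducing 380.** This cannot be done directly, because no SD is given. The SD can be solved for under each meaning of 380, with z = 1.960 + 1.282 = 3.2415:

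- Total of two areas (190 each): SD = 32 / (3.2415 × √(2/190)) = 96.2
- Per area (380 each): SD = 32 / (3.2415 × √(2/380)) = 136.1
- Single group before/after: SD = 32 × √380 / 3.2415 = 192.4

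A one-sided alpha would give 106.6, 150.7 and 213.2.

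**2. Difference-in-difference with 300 per area, no loss, no clustering.** Power = Φ(32/SE − 1.96), with SE = SD × √(2/300).

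| Meaning of 380 | SD of change | SE | Power | Total needed for 90% |
|---|---|---|---|---|
| Two-area total | 96.2 | 7.85 | 98% | 380 |
| Per area | 136.1 | 11.11 | 82% | 760 |
| Single group before/after | 192.4 | 15.71 | 53% | 1,520 |

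Only the first reading reaches 90%. The remaining steps use it.

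**3. The surplus.** 600 − 380 = 220. Loss alone may reach 1 − 380/600 = 36.7%. A design effect alone may reach 600/380 = 1.58.

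**4. Largest ICC that keeps 90% power.** With N analyzed and m = N/4 per neighborhood, the design effect is 1 + (m − 1) × ICC and may not exceed N/380. So ICC ≤ (N/380 − 1)/(m − 1):

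- No loss: N = 600, m = 150; 0.579/149 = 0.0039
- 20% loss: N = 480, m = 120; 0.263/119 = 0.0022
- 30% loss: N = 420, m = 105; 0.105/104 = 0.0010

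**5. Power over the assumed range.** SE = 96.2 × √(2 × design effect / (N/2)). The first figure uses the normal approximation. The second uses a t reference with 4 − 2 = 2 df, as in a neighborhood-level test.

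| Loss | ICC 0 | ICC 0.005 | ICC 0.01 | ICC 0.02 |
|---|---|---|---|---|
| 0% | 98.3 / 57.7 | 87.0 / 40.2 | 73.3 / 31.4 | 53.3 / 22.4 |
| 20% | 95.4 / 50.3 | 82.3 / 36.7 | 69.2 / 29.3 | 50.9 / 21.5 |
| 30% | 92.6 / 46.1 | 79.0 / 34.5 | 66.5 / 28.0 | 49.3 / 20.9 |

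(Power in %.) The 57.7% in the first cell arises with every participant retained and no clustering. It comes from the 2 df alone.

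**The case against.** Several stronger readings are tempting, and the document does not support them.

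- **That nothing is left for loss.** A reader might infer this because no retention figure appears. But 600 are recruited against 380 required, and on the two-area reading 30% loss with no clustering still leaves 93% power. The margin is unexplained, not absent. Nor does the document predict heavy loss: the hard-to-reach remark under Discussion, Study design concerns recruitment, and gentrification is listed as a possibility to examine.
- **That the calculation addresses the wrong contrast.** The effect is worded as an increase after a new route, which suggests a before/after estimate. That wording does not exclude a controlled one. If 380 already compares change between two areas, no further inflation is needed for the difference-in-difference.
- **That 380 is wrong.** It cannot be reproduced, which is different. An article may leave the SD and sidedness to the full protocol, so their absence alone is not the fault.
- **That true power is 66 to 79%.** Those cells combine a back-solved SD, assumed 30% loss, assumed ICCs and a normal approximation that is too favorable with 2 df. They show sensitivity and do not estimate this study's power.

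It is also fair that the article concedes there is little precedent for such calculations, presents walking as an example, names no single confirmatory test and plans multilevel models. The 2 df figures apply to a neighborhood-level test, which it does not specify.

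These points narrow the concern without removing it. The article still draws an unconditional conclusion of sufficiency from a figure with no stated clustering allowance, for a design with two neighborhoods per condition. Multilevel models at the analysis stage do not repair a size claim made without them.

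**Conclusion.** The sufficiency claim is not supported for the stated design. It holds only if 380 is the two-area total and the ICC of change is nearly zero: at most 0.0039 with no loss, falling to 0.0010 with 30% loss. The surplus can absorb moderate loss or slight clustering, but not both. On either of the other two meanings of 380, power for the difference-in-difference is 82% or 53% before any loss or clustering. Extending one walking effect to health-risk behaviors in general has no calculation behind it.

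The clustering part is the firmest, because recruiting more residents cannot remove the limit set by two neighborhoods per condition. The size of the shortfall is uncertain: it depends on what 380 counts, on an SD that had to be back-solved, and on assumed loss and ICC. This should be fixed, but it is a fault in the justification and does not show that 600 is the wrong target.

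**What to change.** Keep 600 and rewrite the paragraph:

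1. State what 380 counts (total, per area or single group), the SD of change actually used, and whether alpha is two-sided.
2. Recompute power, or the minimum detectable difference, for the difference-in-difference in walking minutes per week over a stated range of T0 to T1 retention and ICC of change.
3. Use a small-cluster reference (2 df) for that calculation, or say explicitly that four neighborhoods limit how far a difference can be attributed to the intervention.
4. Replace the general sufficiency sentence with one limited to walking and to those assumptions. For example: With [n] residents measured at both stages, an SD of change of [x] min/week and an ICC of [range], the difference-in-difference in walking has [range] power to detect 32 min/week; no power is claimed for other behaviors.

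The bracketed values must come from the study team. The back-solved SD of 96 and the 66 to 79% figures should not be entered as study inputs.

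The cost is one paragraph and a short recalculation, with no extra recruitment. The downside is that the stated power will look less favorable.

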**Fig. 3 Fig3:**
[figure not shown]
Flowchart of the survey in the UrbASanté study

### Questionnaire (core data survey)—all participants

A questionnaire-based survey (paper and online versions) will be used to collect self-reported information from individuals regarding socio-demographic characteristics, health outcomes (general health, respiratory health, and weight status), physical activity and sedentary behaviors, perception of neighborhood characteristics, air quality, and noise exposure. The questionnaire includes standardized questions derived from existing validated questionnaires. The questionnaires, the coding procedures, as well as the results of the analyses, will be posted online following an open science strategy using the resources of the Very Large Research Infrastructure called Huma-Num (https://www.huma-num.fr/about-us/), which is supported by the French National Center for Scientific Research (CNRS).

